### Participant recruitment, inclusion and exclusion criteria and randomization

Participants with anxiety disorders and comorbid personality disorders will be recruited from an outpatient clinic. Participation is voluntary. Informed consent is given in writing and signed with a personal signature. Participants may withdraw their informed consent at any time, without any consequences for their treatment. Randomization will take place after informed consent has been obtained. Subjects who meet all of the inclusion criteria will be randomized to two modalities of treatments or to the wait list.

Patients from the wait list will continue pharmacological treatment and will take part in monthly supportive consultations. Crisis intervention will be offered when needed. In accordance with the informed consent procedure, patients will not receive treatment in another clinic while waiting for day-treatment care. After the waiting period they will be randomized into two intervention groups.

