### Assessments

Patients are subjected to four assessments: 1) at the screening; 2) at baseline after randomization; 3) at the end of the 12-week treatment; and 4) six months after the end of therapy in order to evaluate the longer-term effects of the treatments. Patients in the wait-list group will have one additional assessment at the end of the 12-week waiting period.

Information from the screening will be used to perform stratified randomization and to validate the inclusion and exclusion criteria. Patients will be assessed by independent and trained clinicians who will remain blind to the treatment conditions, and who will not be involved in direct clinical care of any of the patients. Primary outcome measures and secondary outcome measures can be distinguished in this study. The primary outcome measures include self-report symptoms of anxiety, observer-rated symptoms of anxiety, global improvement, and dichotomized diagnosis of anxiety disorder (improved or unimproved). The secondary outcome measures include personality, depression, self-esteem, defense mechanisms, beliefs about self and others, interpersonal problems, object relations, parental bonding, meta-cognition, and quality of life. The following sociodemographic data will be collected: sex, age, marital status, education, past treatments, symptom history, and medication. We will also examine patients’ expectancy toward change and treatment. Some of the variables, such as the presence or absence of a personality disorder, will be treated in exploratory analyses as predictors and moderators of treatment response. The time points of assessment and measures are presented in Table 3.

**Table 3 Tab3:** Instruments at different assessment points

Instrument	Screening	Baseline	End of Treatment	6-Month Follow-up
STAI		X	X	X
HAM-A		X	X	X
CGI-S		X	X	X
CGI-I		X	X	X
M.I.N.I.	X		X	X
SCID-II	X			
BDI-II	X		X	X
OQ-45		X	X	X
SES		X	X	X
DSQ-40		X	X	X
PBQ		X	X	X
IIP		X	X	X
DWM-S		X	X	X
ECR		X	X	X
BORRTI		X	X	X
MCQ		X	X	X
SWLS		X	X	X
CEQ		X		

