The effects of the intervention on symptoms of anxiety are the primary outcome measures in our study. Although the study’s general aim is to compare both treatments with the wait list, an additional comparison has been planned of both treatments on the outcomes. Comparison between all three groups is possible for two subsequent measurements. Due to ethical reasons, subjects from the wait list will start therapy soon after the second measurements and will not be available to participate in the study during the third measurement. As a result, that data will be analyzed in a 3 × 2 experimental plan (three groups available for two repeated measures) and in a 2 × 3 experimental plan (two groups available for three repeated measures). Based on the trials mentioned above, we assumed that we would be able to show the differences between the interventions and the control conditions with a standardized effect size of 0.58 (the lowest value effect size presented in the literature) for continuous outcomes. As this effect size was Cohen’s d suited for t-test comparisons, we conducted a conversion into f suited for analysis of variance (f = 0.29). The sample size was calculated using the G*power software program [23]. Assuming an alpha of 0.05, with a power (1-β) of 0.80, a minimum number of 96 patients is required for a 2 × 3 experimental plan, and a minimum number of 120 patients is required for a 3 × 2 experimental plan. Furthermore, for the purpose of being able to identify the difference between the two treatments, we followed the design of the most similar study [2] and assumed effect sizes of 0.24 for continuous outcomes, which leads to a total sample size of 171 participants for a 3 × 2 experimental plan and a total sample size of 140 participants for a 2 × 3 experimental plan. We will also test possible within-between group interaction, however its effect size is not available in literature. We assumed a medium effect size for the interaction (f = 0.25), which needs 156 participants in a 2 × 3 plan and 159 participants in a 3 × 2 plan. Assuming that there is a dropout rate of 25 %, this means that 199 participants will need to be recruited.

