### Statistical analysis

All data analyses will be performed using SPSS Statistics software v21.0 (IBM Corporation, Armonk, NY, USA). All randomized patients will be analyzed, including those who stop receiving treatment, on an intention-to-treat (ITT) as well as treatment-completer basis. The multiple imputation method will be used for missing data when appropriate. Analyses of variance with repeated measures (three measurement points: pre, post, and follow-up) will be applied for continuous data (primary outcomes: STAI, HAM-A, CGI-S, and CGI-I; secondary outcomes: BDI-II, OQ-45, SES, DSQ-40, PBQ, IIP, DWM-S, ECR, BORRTI; MCQ, and SWLS). Primary planned comparison is the interaction between the time (pre-to-post and post-to-follow-up change on anxiety) and group variables (CBT versus wait list; PDT versus wait list). Chi-squared tests will be applied for dichotomous data (MINI). Additionally, random effects models for repeated measures will be used. Multiple regression analyses will be applied to test moderators of change that is to show whether each of the interventions is more effective for some groups of patients (interventions, diagnoses, combination of diagnoses and baseline measurements as predictors). Multiple regression analyses will be also applied to search for mediators of change that are theory-specific (for example, changes in beliefs for CBT and changes in defense mechanisms for psychodynamic therapy). We will take into account to what extent the patients were exposed to the intervention by analyzing the dose-effect relationship.

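### The primary comparison includes post-to-follow-up change against a wait list that has no untreated follow-up, so two of its four contrasts cannot be estimated

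*Protocol article*

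**What the plan says.** The Statistical analysis section of the protocol article plans the following for the continuous outcomes: "Analyses of variance with repeated measures (three measurement points: pre, post, and follow-up) will be applied for continuous data". It names as primary planned comparison the "interaction between the time (pre-to-post and post-to-follow-up change on anxiety) and group variables (CBT versus wait list; PDT versus wait list". Missing data are to be handled by multiple imputation where appropriate.

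The Sample size calculation section states that wait-list patients "will start therapy soon after the second measurements and will not be available to participate in the study during the third measurement". It therefore splits the analysis between two layouts: "3 × 2 experimental plan (three groups available for two repeated measures) and in a 2 × 3 experimental plan (two groups available for three repeated measures".

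Two other sections bear on what happens to these patients later. The section on recruitment and randomization says: "After the waiting period they will be randomized into two intervention groups". The Assessments section lists four assessments for patients, among them end of treatment and six months after therapy, and adds: "Patients in the wait-list group will have one additional assessment at the end of the 12-week waiting period".

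**The concern.** The analysis section asks for something that the design section rules out. A post-to-follow-up contrast against wait list needs the change in untreated patients from week 12 to six months after therapy. Under the design, those patients start one of the two therapies soon after week 12, so no such change exists.

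An analyst who follows the text must drop half of the stated primary comparison, fill an empty cell by imputation, or use wait-list patients who have by then been treated. The article does not choose between these, so the choice would fall after the data are in. The last two options could be reported as evidence that gains last relative to no treatment, which the trial cannot show.

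**Working it through.** **1. The plan's own sizes.** They show which layouts were planned. Inputs from Sample size calculation: alpha 0.05, power 0.80, effect sizes 0.29, 0.24 and 0.25. Method: noncentral F with λ = f²N, no gain from repeated measures, N rounded up to equal groups.

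- Group effect, df1 = k − 1, df2 = N − k. At f = 0.29, two groups need 96 (λ = 0.0841 × 96 = 8.07) and three groups need 120 (λ = 10.09). At 0.24 used as f, they need 140 (λ = 0.0576 × 140 = 8.06) and 171 (λ = 9.85).
- Interaction, df1 = (k − 1)(m − 1), df2 = (N − k)(m − 1), f = 0.25. The 2 × 3 plan needs 156 (λ = 0.0625 × 156 = 9.75) and the 3 × 2 plan needs 159 (λ = 9.94).

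All six sizes match the article. The total also matches the 3 × 2 interaction: 159 × 1.25 = 198.75, or 199. (Whether that is the right way to allow for dropout is a separate matter.) No size refers to three groups at three times.

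**2. Which cells are observed.**

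| Group | Pre | Post (12 weeks) | Follow-up |
|---|---|---|---|
| Cognitive-behavioral (C) | yes | yes | yes |
| Psychodynamic (P) | yes | yes | yes |
| Wait list, untreated (W) | yes | yes | none |

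**3. Which contrasts can be estimated.** Write μ(g,t) for the mean of group g at time t. The nine-mean model with the W follow-up cell empty has rank 8. A contrast is estimable only if adding it as a row leaves the rank at 8.

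| Contrast | Expression | Estimable |
|---|---|---|
| C vs W, pre-to-post | [μ(C,2) − μ(C,1)] − [μ(W,2) − μ(W,1)] | yes |
| P vs W, pre-to-post | [μ(P,2) − μ(P,1)] − [μ(W,2) − μ(W,1)] | yes |
| C vs W, post-to-follow-up | [μ(C,3) − μ(C,2)] − [μ(W,3) − μ(W,2)] | no |
| P vs W, post-to-follow-up | [μ(P,3) − μ(P,2)] − [μ(W,3) − μ(W,2)] | no |
| C vs P, post-to-follow-up | [μ(C,3) − μ(C,2)] − [μ(P,3) − μ(P,2)] | yes |

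The first four rows are the stated primary comparison, so 2 of 4 are lost. The fifth row is available but is not part of that comparison.

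**4. How many patients are affected.** The allocation ratio is not stated. The wait list is 199/3 ≈ 66 patients at 1:1:1, or 199/5 ≈ 40 at 2:2:1. The follow-up cell is empty for all of them, so no observed untreated value can inform an imputation.

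**5. Why the later fate of these patients should be stated.** After 25% dropout, the initially allocated therapy arms hold 199 × 2/3 × 0.75 ≈ 100 patients at 1:1:1, or 199 × 4/5 × 0.75 ≈ 119 at 2:2:1. If re-randomised patients count, the total is at most 199 × 0.75 ≈ 149. If the wait list loses 25% in each phase, it is about 137 (99.5 + 66.3 × 0.75²) or about 142 (119.4 + 39.8 × 0.75²). The article's 2 × 3 sizes are 140 and 156, so it matters whether these patients are meant to be in that plan.

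**The case against.** The strongest reply is that the authors saw the limit. The Sample size calculation section already gives the workable layout, and the analysis section squeezes two plans into one badly worded sentence. That is largely right, and it makes the remedy small. It does not remove the error: the sentence is the one that defines the primary comparison, and it attaches both time changes to the wait list.

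It is also fair that the damage is limited. Both pre-to-post contrasts stand, and they serve the first objective. Long-term effectiveness appears under Objectives only for the two active treatments. A reader might infer that the whole primary comparison fails; the documents do not support that. A reader might also infer that the sponsor intends to impute the empty cell. The text says only that imputation is used where appropriate; it neither plans nor excludes this.

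A further tempting reading is that the plan throws away up to a third of the randomised patients, and with them the power of the therapy comparison. This is not established, for three reasons:

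- The sections conflict. Assessments suggests that these patients are followed after therapy; Sample size calculation says they are unavailable at the third measurement. If the latter governs, there are no follow-up data to discard. No section says whether their later data are used.
- Analysing only the initially allocated arms is legitimate. A second wave has been through a 12-week wait with supportive consultations, and its treatment effect may differ. Table 3 has no end-of-wait column to show which instruments would serve as its baseline.
- The power loss depends on unstated inputs. With about 100 patients (1:1:1) and 0.24 read as f, power for the between-group test is 0.66 without any repeated-measures gain. It is 0.72, 0.76 or 0.83 if the correlation between measurements is taken as 0.8, 0.7 or 0.5.

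**Conclusion.** The primary planned comparison is wrong as written. Two of its four contrasts, post-to-follow-up change for each therapy against wait list, have no untreated control data and cannot be estimated. This follows from the article's own statements and needs no assumption about allocation, dropout or effect size. Multiple imputation does not repair it, since the cell is empty for the whole arm by design. Values collected later would compare treated patients with treated patients. The pre-to-post contrasts against wait list and the follow-up contrast between therapies are sound.

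Separately, the sections on recruitment and randomization, Assessments, and Sample size calculation do not agree on what is measured in re-randomised wait-list patients. This is a contradiction to resolve, not proof that data are discarded. The headcounts given for it depend on an assumed allocation ratio and on the article's 25% dropout.

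**What to change.** Reword the Statistical analysis section to match the two layouts under Sample size calculation:

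- Primary comparison: pre-to-post change in anxiety, each therapy versus wait list, in the 3 × 2 plan. State that no wait-list value beyond the 12-week assessment is imputed or used in it.
- Post-to-follow-up change: psychodynamic versus cognitive-behavioral therapy only, in the 2 × 3 plan.

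Reconcile the three sections on whether re-randomised wait-list patients are assessed at the end of therapy and at six months, and state whether their data enter the therapy-versus-therapy comparison. Leaving them out is acceptable if stated. If they are pooled, name the end-of-wait assessment and its instruments as their baseline, include randomisation wave in the model, and say how a difference in treatment effect between waves will be examined.

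The Trial status section puts the start of recruitment after publication, so at that stage the correction to the primary comparison costs only wording. Pooling, if chosen, would add some analysis and assessment detail.

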The inclusion and exclusion criteria are listed in Table 1. The number of excluded patients and the reasons for exclusion will be recorded. The diagnostic criteria are based on the DSM-V system. Initial assessment will be conducted with independent researchers who will not be involved in the further interventions. It will include a pharmacological consultation by a psychiatrist, personality diagnosis with SCID-II [24, 25], and diagnosis of clinical disorders with the Mini International Neuropsychiatric Interview 5^1^ (MINI) [71, 51]. Diagnosis and evaluation for treatment will be carried out during ambulatory sessions. The focus of the treatment is on psychotherapy, but medication will be continued or initiated if necessary during the screening procedure at least four weeks before the beginning of group psychotherapy (stable medical treatments with selective serotonin re-uptake inhibitors or serotonin-norepinephrine reuptake inhibitors, without dose changes during psychotherapy unless necessary). Baseline measurements and final adjustments of pharmacological treatment will be conducted one day before the beginning of therapy. Randomization will take place during the last diagnostic session. Participants will be randomized using random number tables. A recruitment flow chart is presented in Fig. 1. Patients are planned to be enrolled in the study for over a period of three years. Before participating in the study, each patient will be provided with written information about the study and will be invited to give written consent for inclusion. Participants who do not meet the inclusion criteria will be offered suitable alternative treatment options.

**Table 1 Tab1:** Inclusion and exclusion criteria

Inclusion criteria	Current diagnosis of Axis I anxiety disorder (based on the MINI)
	Diagnosis of comorbid personality disorder (based on the SCID II) or depressive disorder (based on the MINI)
	Aged 18 to 65-years-old
	Sufficient knowledge of the Polish language
	Written informed consent from the patient
Exclusion criteria	Organic brain disorder
	Acute substance-related disorders
	Schizophrenia or bipolar affective disorder
	Severe depression (defined as over 26 points on the Beck Questionnaire)
	Cluster A personality disorders
	Current suicidal ideation and a high risk of suicide
	Restricted intellectual capacity
	Serious unstable medical problems or complications
	Concurrent psychotherapeutic treatment

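### The MINI diagnosis, a primary outcome, is assigned an unadjusted chi-squared test that is valid but leaves screening data and stratification unused; an adjusted logistic model would be a cheap, modest gain

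*Protocol article*

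**What the plan says.** Under Assessments, the primary outcomes include "global improvement, and dichotomized diagnosis of anxiety disorder (improved or unimproved"). Under Statistical analysis, the continuous primary outcomes go to repeated-measures analysis of variance, while for the diagnosis the article says "Chi-squared tests will be applied for dichotomous data (MINI"). No covariate, stratum or binary-outcome model is named for it. One further sentence, "Additionally, random effects models for repeated measures will be used", is not tied to the MINI, and multiple regression is reserved for moderators and mediators.

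Three other statements bear on the point:

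- Table 1 requires "Current diagnosis of Axis I anxiety disorder (based on the MINI"), so every patient has the condition at entry.
- Table 3 places the MINI, SCID-II and BDI-II at screening, and the Assessments section says "Information from the screening will be used to perform stratified randomization and to validate the inclusion and exclusion criteria". The article does not name the stratification factors.
- Randomized patients are analysed "on an intention-to-treat (ITT) as well as treatment-completer basis", and "The multiple imputation method will be used for missing data when appropriate".

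**The concern.** The continuous primary outcomes enter the repeated-measures analysis with their own pre-treatment score. The MINI outcome cannot, because its baseline value is the same for everyone. Any pre-treatment information must come from other variables, and the chi-squared test admits none.

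Such variables exist. The MINI gives the number and type of anxiety disorders, the BDI-II depressive severity, and the SCID-II personality-disorder status, all before allocation. The article itself treats diagnoses and baseline measurements as candidate predictors of response. It also randomizes within strata formed from screening data, and a test that ignores prognostic strata tends to be conservative.

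At stake is some power on one primary outcome, together with an adjusted effect estimate and its interval. The sample size calculation rests on continuous outcomes only, so nothing in it secures power for the MINI.

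**Working it through.** **Inputs from the article.** Total N is 199 (159 × 1.25 = 198.75), with three arms, 25% dropout and alpha 0.05. The allocation ratio is not stated. Assuming equal arms, 199/3 ≈ 66 per arm and 66 × 0.75 = 49.5 ≈ 50 after dropout. There is no MINI rate, power or sample size in the article to reproduce, so all recovery rates and covariate strengths below are assumptions.

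**Step 1: power of the chi-squared test.** For n per arm and rates p0 and p1 with mean p, power = Φ{(|p1 − p0| − 1.96·s0)/s1}, where s0 = √[2p(1−p)/n] and s1 = √[(p0(1−p0) + p1(1−p1))/n].

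For 25% versus 50% with n = 50:

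- s0 = √(2 × 0.375 × 0.625/50) = 0.0968
- s1 = √((0.1875 + 0.25)/50) = 0.0935
- power = Φ{(0.25 − 0.1898)/0.0935} = Φ(0.64) = 0.74

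Other assumed rates:

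| Recovery | 66 per arm | 50 per arm |
|---|---|---|
| 20% vs 40% | 71% | 59% |
| 20% vs 50% | 96% | 89% |
| 30% vs 50% | 65% | 53% |
| 40% vs 50% | 21% | 17% |

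**Step 2: gain from adjustment at 50 per arm, 25% versus 50%.** Simulation compared the chi-squared test with covariate-adjusted logistic regression. When screening covariates explain 0%, 10%, 20% and 30% of the latent variance, power rises by about 0, 2, 5 and 9 points. Other runs of the same comparison gave up to 4 points at 10% and up to 7 at 20%, so differences of a point or two should not be read closely. At 66 per arm the gain over 10% to 30% was 3 to 6 points.

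**Step 3: a second set of assumptions.** Here there are 66 per arm, a conditional treatment log odds ratio of 1.0, one stratum and one continuous covariate.

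| Prognostic strength (stratum OR; covariate OR per SD) | Chi-squared | Adjusted logistic |
|---|---|---|
| None | 78–79% | 78% |
| Weak (2.0; 1.4) | 74–75% | 76% |
| Moderate (4.1; 2.0) | 64% | 71% |
| Very strong (8.2; 2.9) | 49–50% | 64% |

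The chi-squared column falls because the marginal contrast shrinks as unmodelled heterogeneity grows. Adjustment recovers part of that.

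**Step 4: error rate.** With no effect, the chi-squared test rejected in 4.9–5.6% under simple randomization and in 5.2% down to 3.6% under stratified randomization. The adjusted logistic test rejected in 4.9–5.4% at 66 per arm and in roughly 5–6% at 50 per arm.

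**Step 5: imputation.** With 16 of 66 outcomes per arm imputed, 20 imputations and no effect, chi-squared statistics pooled by the D2 rule rejected in 4.9–5.0%. A risk difference pooled by Rubin's rules rejected in 5.0–5.1%.

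**The case against.** The strongest defence is that an unadjusted chi-squared test is a sound analysis of a randomized binary outcome, so preferring a model is a choice about efficiency. That stands. The article also makes the time-by-group interaction on anxiety its primary planned comparison, so the MINI test carries less weight than the continuous analyses.

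The covariates may also be weak. Table 1 excludes BDI-II scores above 26, which narrows that scale. In the team's earlier day-clinic sample 82.3% had a personality disorder, so that status may vary little. The Background calls the evidence on comorbidity and outcome inconsistent. The count of anxiety disorders is prognostic by construction only if improvement means that none remains, and "dichotomized diagnosis of anxiety disorder (improved or unimproved") does not settle that. These reasons put the lower end of the gain in play, but adjustment costs little even then.

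Three stronger readings might be inferred, and the documents do not support them:

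- **That chi-squared results cannot be combined across imputations.** They can, by the D2 rule or through the underlying risk difference. The article states no pooling rule, but that detail may properly sit in the full plan.
- **That the test risks false positives.** Averaging the statistics (10.0–10.5%), taking the median p-value (8.9–9.5%) or using one completed data set (11.8–12.6%) would inflate the error rate, but the article plans none of these.
- **That dropout makes the test invalid.** A chi-squared test restricted to completers rejected in 5.5–13.7% when dropout depended on a prognostic covariate differently by arm. That comes from an assumed selection pattern. The plan pairs the completer analysis with intention-to-treat and imputation, for which the pooled chi-squared test stayed at 5.0–6.0%.

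**Conclusion.** The point holds as a modest efficiency improvement. The only test named for the MINI primary outcome ignores prognostic data already collected before allocation and the stated stratification. At 50 per arm with recovery of 25% versus 50%, the expected gain is about 0 to 2 power points with weak covariates and about 5 to 9 if they explain 20% to 30% of the latent variance. These figures rest on equal allocation, assumed recovery rates and assumed prognostic strength, none of which the article gives. The chi-squared test keeps its nominal error rate, or falls below it when strata are ignored, so there is no error-rate defect to correct. The change is worth making because it is nearly free and yields an adjusted effect estimate with an interval.

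**What to change.** Make the main MINI analysis a logistic regression of improved versus unimproved on arm, with the contrasts CBT versus wait list, PDT versus wait list, and CBT versus PDT. At six-month follow-up only the last applies, since wait-list patients have by then started therapy. Adjust for the stratification factors and a few prespecified screening covariates, for example the number of MINI anxiety disorders, BDI-II score and personality-disorder status. Prefer screening values, because the article places the baseline assessment after randomization. Pool the log odds ratio and its standard error over imputations by Rubin's rules, report the marginal risk difference beside it, and keep the chi-squared table as descriptive.

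The cost is one or two sentences in the analysis section and no new data. The odds ratio becomes conditional on the covariates, which is why the marginal risk difference is needed. The covariate list must stay short: at 25% versus 50% with 50 per arm, a pairwise comparison has only about 12.5 + 25 = 37.5 improved patients.
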